### Criteria for discontinuing or modifying allocated intervention/comparator {15b}

Criteria for discontinuation or modification of the allocated intervention or comparator include safety concerns, serious or persistent adverse events, pregnancy, protocol deviations affecting participant safety, or investigator judgement. Participants may withdraw consent at any time without consequences for further treatment or study participation.

In case of a worsening of disease activity (CDAI increase > 4.5 compared to baseline) at each visit from week 4 onwards or inadequate improvement of the sum of swollen and tender joints (< 20% change compared to baseline) from week 12 onwards, rescue treatment applies according to standard of care (such as switch or add on of conventional synthetic, biologic or targeted synthetic DMARD (cs/b/tsDMARD)). This results in the participant’s early termination from the study. Non-responder imputation will apply to all patients with a premature end of study.

In case of an AE, a diagnostic or therapeutic procedure, an abnormal assessment (e.g. laboratory abnormalities) the MTX dose can be temporarily interrupted or reduced to ≥ 10 mg/week and re-escalated to 25 mg after resolution of the problem. If drug interruption or intermittent reduction is within a timeframe of ≤ 3 weeks, and re-institution of full dose of the study drug is safe according to the decision of the investigator, no permanent study discontinuation is required.

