### Sample size {19}

Based on literature, the primary endpoint (CDAI ≤ 2.8, i.e. remission) is expected to be achieved by 5% of patients included in the p.o. dose arm, and by 20% in the s.c. arm of the trial [14, 32, 33]. Patients will be randomised in a 1:1 ratio, resulting in an expected sample size for the main outcome of 76 per group (based on *χ*^2^ statistics) with 80% power and a two-sided alpha of 0.05. To account for a conservative 16% dropout rate, the study aims to include 182 patients in total.

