## Statistical methods

### Statistical methods for primary and secondary outcomes {27a}

The null hypothesis is as follows: The use of 25 mg SCMTX is not superior to 25 mg POMTX weekly in patients with active RA, previously treated with POMTX.

The primary endpoint, defined as the proportion of patients achieving CDAI remission at week 24, will be compared between treatment groups using a *χ*^2^ test. A Fisher’s exact test will be used if the endpoint occurs in fewer than five patients in any group. Superiority of the subcutaneous MTX arm will be tested at a two-sided alpha level of 0.05.

Secondary categorical outcomes will be analysed using *χ*^2^ tests (or Fisher’s exact tests where appropriate), and non-normally distributed continuous outcomes will be analysed using the Mann–Whitney *U* test. For categorical variables, absolute frequencies and percentages will be reported. Time to CDAI remission will be analysed using Kaplan–Meier curves, reporting medians and interquartile ranges, and compared between treatment groups using a log-rank test.

Secondary endpoints will be tested in a pre-specified stepwise hierarchical order until the first non-significant result is reached. All outcomes tested thereafter will be considered exploratory (hypothesis-generating). The following sequence for secondary endpoint testing will be utilised: Proportion of CDAI remission at week 12 > CDAI low disease activity (≤ 10) at week 24 > CDAI low disease activity (≤ 10) at week 12 > ACR70% response at week 24 > ACR50% response at week 24 > Difference in change of patient global assessment > HAQ-DI > CRP at week 24 respectively. An early analysis of the main secondary endpoints will be performed at week 12. All other secondary outcomes will be analysed exploratorily.

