### Who will be included in each analysis {27b}

Two analysis sets are defined. The (modified) intention-to-treat (ITT) population includes all randomised participants who received at least one dose of study drug and will be used for all primary analyses. Participants will be analysed according to their allocated treatment group. Non-responder imputation will be applied for patients who discontinue the study or are lost to follow-up over the 24-week study period. The per-protocol population comprises participants who received at least one dose of study drug and did not have major protocol violations that could affect evaluation of the treatment effect on the primary objective. Analyses in this population will be performed as secondary analyses. The time-to-event analysis of time to CDAI remission will not follow a strict ITT approach, as the Kaplan–Meier method accounts for participants who discontinue or are lost to follow-up through censoring.

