### How missing data will be handled in the analysis {27c}

For the primary endpoint, non-responder imputation will be applied to all participants who discontinue the study or are lost to follow-up. In time-to-event analyses, missing data due to dropout will be handled by censoring. No additional imputation methods are planned.

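### The time-to-remission analysis censors patients removed for non-response, which is informative censoring, and its planned medians are not expected to be reached at the planning rates.

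*Protocol article*

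**What the plan says.** **Removal for failure (section 15b).** Two response-based criteria lead to rescue treatment. The first is "worsening of disease activity (CDAI increase > 4.5 compared to baseline) at each visit from week 4 onwards". The second looks at joint counts and starts later in the study: "inadequate improvement of the sum of swollen and tender joints (< 20% change compared to baseline) from week 12 onwards". Rescue results in "early termination from the study". The same section then applies non-responder imputation to every patient whose study participation ends prematurely, without limiting this to one endpoint.

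**Time to remission (sections 27a to 27c).** Section 27a: "Time to CDAI remission will be analysed using Kaplan–Meier curves, reporting medians and interquartile ranges", with a log-rank comparison of the arms. Section 27b says that this analysis will not be strictly ITT, because the Kaplan–Meier "method accounts for participants who discontinue or are lost to follow-up through censoring". Section 27c: "In time-to-event analyses, missing data due to dropout will be handled by censoring. No additional imputation methods are planned". None of the three separates removal for treatment failure from other loss.

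**Planning rates (section 19).** Week-24 remission "is expected to be achieved by 5% of patients included in the p.o. dose arm". The rate assumed for s.c. is 20%.

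**Status.** Time to remission is neither an endpoint in Table 1 nor a step in the testing hierarchy of section 27a, so it is exploratory.

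**The concern.** Kaplan–Meier and the log-rank test are valid under censoring only if a censored patient has the same later chance of the event as a comparable patient still followed. Here a patient is censored because disease activity rose or joint counts hardly moved. Swollen and tender joint counts are components of the CDAI, which also defines remission. Such a patient is less likely to remit than those who stay, yet the method redistributes that patient's probability to those who stay.

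Two things follow. The estimated cumulative remission is too high in any arm with failures. If failures are more frequent in one arm, that arm's curve is raised more. If s.c. is the better route, as the trial hypothesises, oral would be expected to fail more often and the distortion would work against s.c. A published curve and log-rank p-value could then disagree with the non-responder primary result for a purely technical reason.

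The second matter is the numerical summary. Medians and interquartile ranges need curves that reach 50% and 75%, and the planning rates are far below that.

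**Working it through.** **1. The plan's own figure.** For 5% versus 20%, pooled χ² without continuity correction, two-sided 0.05, 80% power, mean rate 0.125:

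n = [1.96·√(2·0.125·0.875) + 0.8416·√(0.05·0.95 + 0.20·0.80)]² / 0.15² = (0.9167 + 0.3834)² / 0.0225 = 75.1, so 76 per group. With 16% dropout, 76/0.84 = 90.5, so 91 per arm and 182 in total. The stated sample size is reproduced, and 91 per arm is used below.

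**2. A worked example (counts assumed).** Both arms have 12 remissions in 91 patients (13.2%), at weeks 4, 12, 16 and 24 as 1, 3, 2, 6. They differ only in terminations after weeks 4, 12 and 16: 3, 30, 12 (45 in total) versus 3, 10, 5 (18 in total).

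- 45 terminations: 1 − (90/91)(84/87)(52/54)(34/40) = 21.8%
- 18 terminations: 1 − (90/91)(84/87)(72/74)(61/67) = 15.4%

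The observed remission is identical, and the arm with more failures looks better by 6.4 points.

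**3. Expected bias with equal true remission of 20%.** Failures are a share of all randomised, split 20/60/20 over weeks 4, 12 and 16. With remissions spread evenly (5 per 100 at each visit):

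- 10% failures: 1 − (95/100)(88/93)(77/82)(70/75) = 21.2%
- 40% failures: 1 − (95/100)(82/87)(53/58)(40/45) = 27.3%

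If all remissions fall at week 24, the values are 20/90 = 22.2% and 20/60 = 33.3%. If they fall mostly early, they are 20.6% and 23.6%. With failures kept at risk, the estimate is 20% in every case.

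**4. Log-rank simulations.** 91 per arm, visits at weeks 4, 12, 16 and 24, mostly 4,000 runs. Failure rates, failure timing and remission timing are all assumptions. The spread within a row reflects remission timing and whether failure is a share of all patients or of non-remitters.

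| True remission s.c./oral | Failures s.c./oral | Rejection, censored as planned | Rejection, failures kept at risk |
|---|---|---|---|
| 20% / 5% | 16% / 16% | 88–90% | 88–89% |
| 20% / 5% | 10% / 22% | 83–85% | 87–88% |
| 20% / 5% | 20% / 40% | 79–81% | 89–90% |
| 20% / 5% | 20% / 50% | 63–75% | 89% |
| 20% / 20% | 10% / 10% | 5% | 5–6% |
| 20% / 20% | 10% / 40% | 10–21% | about 5% |

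In the last row nearly all rejections under censoring favour the arm with more failures.

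**5. Medians and quartiles.** At 20% and 5% with failures of 10–50%, the median was reached in 0 of 4,000 runs in either arm. The first quartile was reached in 19–42% of runs in the s.c. arm and never in the oral arm. At 20% true remission, a Kaplan–Meier median appears only if about 60–77% of patients are censored as failures. At 40% ever-remission it needs about 20–39%, and at 50% or more it needs none.

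**The case against.** The case on the other side is substantial, and it limits the point without removing it.

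- **The bias between arms is conditional.** The document states no rescue rate for either arm. Its only attrition figure is 16% dropout, and it does not say whether that includes rescue. At 16% in both arms, power and type I error barely change, although the curve itself is still about 2 points too high (22.1% for a true 20% with even timing). This stands: a reader might infer that the comparison will be distorted, but the document does not establish that.
- **A median that cannot be reached.** A reader might infer this from 5% and 20%. Those are rates of remission status at week 24, whereas this analysis counts first remission at any visit. Entry requires only CDAI above 2.8 with one swollen joint, and all patients start with a glucocorticoid course, so ever-remission could be higher. No figure for it is given. All that is supported is that a median is not expected at the planning rates.
- **No usable result.** This also goes too far. The curves and log-rank test are planned too, and they are informative once the censoring is corrected.
- **The departure is disclosed.** Section 27b says the analysis is not strictly ITT, and section 27c ties non-responder imputation to the primary endpoint. That softens the conflict with section 15b, whose wording nevertheless covers every premature end of study. Disclosure does not make the stated reason correct.
- **Low stakes.** The analysis is outside Table 1 and the hierarchy. If oral fails more often, the bias runs against s.c. and would not create a false claim of superiority.
- **Adverse-event discontinuations.** Counting these as never remitting is a choice of estimand, not a correction. This stands, and the fix leaves the choice open.

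**Conclusion.** The concern holds in a limited form. The plan writes informative censoring into the time-to-remission analysis and defends it with an incorrect statement. It also departs from section 15b's general non-responder rule for the same patients. Overstatement of cumulative remission follows whenever failures occur among patients not yet in remission who would not have remitted. A distortion between arms needs unequal failure rates, and its size is an assumption throughout:

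- negligible at 16% in both arms;
- a few points of power at 10% s.c. versus 22% oral;
- about 10 points at 20% versus 40%;
- a type I error of about 10–21% at equal true remission of 20% with failures of 10% versus 40%.

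At the planning rates, a median is not expected in either arm and the full interquartile range is not estimable. The primary endpoint, which uses non-responder imputation, is untouched. The change is worth making because it removes a bias from a result that will be read beside the primary one, but it does not threaten the trial's main conclusion.

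**What to change.** In the time-to-remission analysis:

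1. Keep patients terminated for treatment failure in the risk set without an event to week 24, or treat termination as a competing event (Aalen–Johansen cumulative incidence with Gray's test).
2. Censor only loss unrelated to response. State explicitly how discontinuations for adverse events are handled, and run a sensitivity analysis with the alternative handling.
3. Report cumulative remission at weeks 4, 12, 16 and 24 with 95% CI, in place of or in addition to medians and interquartile ranges.
4. Delete the statement in section 27b that Kaplan–Meier deals with discontinuation through censoring, and align sections 15b, 27b and 27c on which analyses use non-responder imputation.

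The cost is wording in the protocol and SAP plus a small programming change. It needs no new data, although the recorded reason for termination must be used to classify each case. The last patient's first visit is planned for the end of November 2026 and the last visit for May 2027, so this can be settled before the final data are available.

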### How missing data will be handled in the analysis {27c}

For the primary endpoint, non-responder imputation will be applied to all participants who discontinue the study or are lost to follow-up. In time-to-event analyses, missing data due to dropout will be handled by censoring. No additional imputation methods are planned.

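### The sections disagree on how far non-responder imputation reaches; read literally, the missing-data section leaves the secondary hierarchy partly resting on patients who were not removed for failure

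*Protocol article*

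**What the plan says.** All references are to the protocol article.

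- **Removal of failures {15b}.** A patient whose CDAI rises by more than 4.5 over baseline (from week 4), or whose summed swollen and tender joints improve by less than 20% (from week 12), gets rescue treatment and leaves the study. The section then says: "Non-responder imputation will apply to all patients with a premature end of study".
- **After leaving {34}.** One voluntary visit four weeks after stopping study drug is described. No week-24 assessment is required.
- **Analysis sets {27b}.** Non-responder imputation is given for patients who discontinue or are lost over the 24 weeks, without naming an endpoint.
- **Missing data {27c}.** Non-responder imputation is given for the primary endpoint and censoring for time-to-event analyses, followed by "No additional imputation methods are planned".
- **Secondary hierarchy {27a}.** The order is: (1) CDAI remission at week 12, (2) low disease activity at week 24, (3) low disease activity at week 12, (4) ACR70 and (5) ACR50 at week 24, then steps 6 to 8: "Difference in change of patient global assessment > HAQ-DI > CRP at week 24 respectively".
- **Test for continuous outcomes {27a}.** The only one named is conditional: "non-normally distributed continuous outcomes will be analysed using the" Mann–Whitney test. Baseline adjustment is not mentioned.

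**The concern.** Two things follow if {27c} is taken at its word.

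First, the denominators of steps 1 to 5 depend on which section the analyst follows. Under {15b} and {27b}, a patient terminated for inefficacy counts as a non-responder. Under {27c} that patient has no value and no imputation, and drops out. Because testing stops at the first non-significant step, the choice can decide what is confirmatory.

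Second, non-responder imputation cannot supply a change in HAQ-DI, and {27c} plans nothing else. A test that needs one week-24 value per patient would then compare groups selected after randomisation by how the patients were doing. If more oral patients are removed for failure, the remaining oral patients look better than the randomised arm and the contrast shrinks.

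**Working it through.** **1. The plan's own figure.** The inputs are in the sample size section {19}: remission "expected to be achieved by 5% of patients included in the p.o. dose arm, and by 20% in the s.c. arm", "with 80% power and a two-sided alpha of 0.05", and 1:1 allocation.

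n = [1.960·√(2·0.125·0.875) + 0.842·√(0.05·0.95 + 0.20·0.80)]² / 0.15² = 75.1, so 76 per group.

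76 / 0.84 = 90.5, so 91 per group and 182 in total. The stated figure reproduces. It covers the primary endpoint only. The article gives no SD, effect size or removal rate for the continuous endpoints, and does not say whether the 16% dropout includes rescue terminations. Everything below therefore rests on assumptions.

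**2. Binary endpoints: does the reading matter?** The counts are assumed. Take week-24 low disease activity in 30 of 91 oral and 45 of 91 s.c. patients (χ² without continuity correction).

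| Reading | Terminated (oral, s.c.) | Oral | s.c. | p |
|---|---|---|---|---|
| Non-responder imputation | any | 30/91 = 33% | 45/91 = 49% | 0.024 |
| {27c} literally | 30, 18 | 30/61 = 49% | 45/73 = 62% | 0.148 |
| {27c} literally | 15, 15 (about 16% per arm) | 30/76 = 39% | 45/76 = 59% | 0.015 |

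The same responders pass or stop the hierarchy at step 2, depending on the section followed. With unequal removal the literal reading weakens the result; with equal removal it strengthens it.

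**3. Continuous endpoints: how much of the effect is kept?** Let the change (improvement positive, in SD units) be N(0,1) in the oral arm and N(d,1) in the s.c. arm. Patients below one common threshold t on an early-response index, correlated ρ with the change, are removed. With φ the normal density and Φ the distribution function, the mean among those kept in an arm with mean μ is

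μ + ρ·φ(t−μ) / [1−Φ(t−μ)].

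Example: d = 0.5, ρ = 0.7, 16% of the oral arm removed, t = −0.994.

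- Oral: 0.7 × 0.2433/0.84 = 0.203.
- s.c.: 0.5 + 0.7 × 0.1306/0.9325 = 0.598.
- Difference 0.395, which is 79% of 0.5.

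Share of the true effect kept:

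| ρ | d | 16% of oral removed | 30% | 40% |
|---|---|---|---|---|
| 0.5 | 0.3 | 84% | 77% | 73% |
| 0.5 | 0.5 | 85% | 78% | 74% |
| 0.7 | 0.3 | 77% | 67% | 62% |
| 0.7 | 0.5 | 79% | 69% | 64% |

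At ρ = 0.9 the range runs lower, from 73% down to about 51%. Simulation with 2,000,000 patients per arm agrees to within about one percentage point. With 91 randomised per arm and 16% of the oral arm removed, power over ρ = 0.5 to 0.9 falls from 0.92 to 0.76–0.80 (d = 0.5) and from 0.53 to 0.34–0.38 (d = 0.3). This includes the loss of patients as well as the bias.

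**4. Is the direction fixed?** No.

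- With ρ = 0 there is no bias: 0.50 is recovered for d = 0.5.
- If 16% of s.c. patients leave for inefficacy (ρ = 0.7) while oral dropout is unrelated to response, the bias is 0.7 × 0.2433/0.84 = 0.20 SD in favour of s.c., even with no true effect.

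**5. Baseline adjustment.** With equal variances and baseline–follow-up correlation r, the variance of the adjusted mean difference relative to the change-score difference is (1−r²)/[2(1−r)] = (1+r)/2. This gives 0.65, 0.75 and 0.85 for r = 0.3, 0.5 and 0.7. It compares mean-based analyses and says nothing about a rank test.

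**The case against.** A reader might infer that the continuous endpoints are fixed as an unadjusted Mann–Whitney test on completers, biased towards no difference. The document does not support that much:

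- A completers-only analysis is an inference. A likelihood-based repeated-measures model is not imputation, so {27c} does not exclude one, and the analysis plan is not shown.
- Mann–Whitney is named only for non-normal outcomes. The article does not say what is done otherwise.
- Not every failure lacks a week-24 value. The schedule of assessments checks both rules at week 24 too, and a patient who first meets one there has been assessed. Likewise, before week 12 only the worsening rule operates, so the week-12 endpoints are less exposed.
- The direction is conditional. {15b} also lists safety reasons for stopping, and these may differ by arm.
- The sizes come from assumed inputs, several with more removal than the plan's 16%.
- Steps 6 to 8 are confirmatory only if the five earlier secondary tests succeed.

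All of this stands and limits the point. It does not remove it. The conflict over the scope of non-responder imputation is in the article's own text and reaches steps 1 to 5. The closing sentence of {27c} is a positive statement, not silence left to the analysis plan, and followed as written it leaves terminated patients without a defined place in the secondary analyses.

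**Conclusion.** The point holds in a limited form. {15b} and {27b} contradict {27c} on which endpoints receive non-responder imputation, and no rule is given for patients terminated before week 24 in the three continuous endpoints of the hierarchy.

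The literal reading of {27c} may bias these comparisons. The likeliest direction is towards no difference, provided s.c. is better and removal is for inefficacy under a similar process in both arms. Other dropout patterns remove or reverse the bias. Under a common removal threshold, with 16 to 40% of the oral arm removed and ρ of 0.5 to 0.7, about 60 to 85% of the true effect is kept. These figures are illustrative and are not estimates for this trial.

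The primary endpoint has explicit non-responder imputation and is unaffected. This should be corrected before the final analysis, but it does not threaten the trial's main result.

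**What to change.** 1. **Binary endpoints.** Amend {27c} so that non-responder imputation covers every binary responder endpoint in the hierarchy (CDAI remission at week 12, low disease activity, ACR70, ACR50), in line with {15b} and {27b}.
2. **Continuous endpoints.** For patient global assessment, HAQ-DI and CRP, analyse the modified ITT set with a repeated-measures model using all scheduled visits up to termination, adjusted for baseline value and centre. The variance gain in step 5 of the working belongs to this adjusted model. HAQ-DI is scheduled only at baseline and weeks 12 and 24, so a patient terminated at week 4 contributes no later value.
3. **Sensitivity analysis.** Add a worst-rank analysis in which patients terminated for rescue or lack of efficacy receive the worst rank. It answers a composite question and is harder to interpret, so it supports the model and does not replace it.

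The cost is protocol and analysis-plan wording and slightly more programming, with no added patients or visits and no change to the rescue rules. The downside is that the model assumes data are missing at random given the observed visits, which is why the sensitivity analysis is needed. The last patient's visit is expected in May 2027, so there is time to settle this first.
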